### Study design and randomisation

The study design is a community-based, two-arm cluster RCT. We will assess the impact of UCT interventions on the risk of child undernutrition among households targeted for intervention and also in the community in which the interventions are implemented. A clustered design is necessary to ensure feasibility of delivery of the interventions being tested and to prevent contamination. The unit of randomisation will be the cash distribution point; i.e. one or more villages grouped to receive cash in a given location. Households will be assigned to the trial arm on the basis of their village of residence. The randomisation will be undertaken in a public meeting to which the village leaders will be invited. The names of the villages and their cash distribution point will be written on pieces of paper placed in sealed envelopes of identical shape size and colour. Meeting participants will be invited to blindly select envelopes one by one which will be sequentially allocated to the modified and standard cash arms, until all have been allocated. There will be around 20 cash distribution points, which will result in each intervention group having 10 clusters that will contain around 20 villages.

Cash receiving households will be exhaustively sampled from the selected villages for inclusion in the study cohort. In addition, a sample of households not eligible for cash transfers will be randomly sampled for inclusion in the cohort, from the same villages. The study participants will be children 6–59 months and women 15–49 years, exhaustively sampled from the selected households. The target number of participants is 3,500 children (6–59 months) and 2,500 women (15–49 years). Disabled and seriously sick individuals will be excluded.

Questions related to household costs and income will be included in the endline cohort questionnaire. For collection of qualitative data on household and community costs, up to 10 villages will be selected purposively using selection criteria (e.g. village size, whether village is located at a distribution point, remoteness of village, receipt of standard or modified intervention) to ensure a wide range of village characteristics are represented in the sample. Up to nine participants for the focus group discussions will then be selected randomly from amongst the programme beneficiaries in each village.

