### Sample size calculation

In order to detect a difference of 5 percentage points in the prevalence of acute malnutrition among children 6–59 months of age between the trial arms, assuming a fixed number of 20 clusters and end-line prevalence of 21 %, and allowing a type 1 error rate of 5 % and power of 80 %, we calculated that a minimum sample size of 1,767 children in 10 clusters for each arm will be necessary. Because the clustered sample design will induce correlation within sampling units, we used a sample size calculation method designed for use with clustered RCTs [28]. We also accounted for variable numbers of children served by each distribution point in calculating our final sample size.

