### Data analyses

We will test for an end-line difference in the prevalence of acute malnutrition, among children 6–59 months, between the cash receiving households in the two study arms. Analysis will be conducted using generalized estimating equations (GEE) and adjusted for correlation of responses within clusters. We will choose our covariates and identify potential confounders using the pathways described in the theory of change (Fig. 1), and explore the intervention’s mechanisms of action. We will also undertake post hoc analyses by age strata, <24 months and ≥24 months. We will also test for an end-line difference in acute malnutrition prevalence between non-beneficiary households in the two arms of the trial, to assess the impact of the modified intervention at a population level.

Formative research data about context will be synthesized into a narrative report, which will be updated as contextual changes occur. Qualitative data from the longitudinal and focused studies will be analysed using descriptive content analysis, comparing views from different participants within each intervention group in the trial and members of non-cash receiving households to assess the extent of triangulation and explore how the intervention receipt affected different participants. Researchers will discuss emergent themes, and coding structures will be developed from these themes and from the research questions. Data will then be coded in NVivo V10. Data will be summarised and described using illustrative quotes. Longitudinal qualitative data collection will be analysed between data collection points, to build our theory of how the intervention is working or not working. We will discuss and validate the development of our theory of change and research findings with a sample of research participants and team members at two time points, one during the intervention implementation, and one after the UCT has ceased.

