### Ethical considerations

The study protocol was approved by two independent ethics committees; the Comité Consultatif National d'Ethique at the Ministry of Health in Niger (ID number 021/2014/CCNE).and the University College London Research Ethics Committee (project ID 6543/001). This study is also registered with ISRCTN (ISRCTN25360839). Informed consent procedures described above will allow individual participants to decline to participate. Regardless of whether potential participants consent to take part in the study, the study teams will offer to screen women and children in the sampled households for acute malnutrition and anaemia and refer them to health facilities for treatment according to local diagnostic criteria.

Trial safety will be monitored by measuring MUAC in children brought to the cash distributions in June and July. Our stopping rule will be a significant difference of ≥5 percentage points in the prevalence of low MUAC between arms at either time point, with a *p* < 0.001. Analysis will be conducted using the Wald chi-square test in Stata 13, adjusted for cluster, age, and sex.

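### With 20 clusters, GEE without a small-sample correction has a true type 1 error of about 7–10%, not 5%, and the Wald chi-square named for safety monitoring is too lenient at p < 0.001

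*Protocol article*

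**What the plan says.** All of this is in the protocol article.

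- Study design and randomisation: "There will be around 20 cash distribution points, which will result in each intervention group having 10 clusters". Data analyses takes the primary contrast at end-line in cash-receiving households only, with a second contrast in non-beneficiary households.
- Sample size calculation: the figure is derived "assuming a fixed number of 20 clusters and end-line prevalence of 21"%, "allowing a type 1 error rate of 5 % and power of 80"%, to "detect a difference of 5 percentage points in the prevalence of acute malnutrition among children 6–59 months of age between the trial arms". The result is "a minimum sample size of 1,767 children in 10 clusters for each arm will be necessary". The section says that unequal cluster sizes were allowed for, but gives no coefficient of variation (CV) and no intracluster correlation (ICC).
- Data analyses: "Analysis will be conducted using generalized estimating equations (GEE) and adjusted for correlation of responses within clusters". No variance estimator, reference distribution, degrees of freedom or small-sample correction is named, and none is ruled out.
- Ethical considerations: the trial stops if low MUAC prevalence differs between arms by at least 5 percentage points with p < 0.001, in June or in July. For that test, "Analysis will be conducted using the Wald chi-square test in Stata 13, adjusted for cluster, age, and sex".

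**The concern.** The usual GEE robust variance is justified as the number of clusters grows, not the number of children. With 10 clusters per arm two things go wrong together: the sandwich variance is biased downward, and a normal or chi-square reference ignores that only 20 − 2 = 18 degrees of freedom lie between clusters. Unequal clusters, which the article expects, make the bias worse. Confidence intervals become too narrow, and a difference in either direction is declared more often than the stated 5%.

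The monitoring test sits far out in the tail, where the same fault is proportionally larger. Adjustment for cluster cannot rescue it through cluster fixed effects, because arm is constant within a cluster. A false crossing there would stop the trial.

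**Working it through.** **Inputs.** From the article: 20 clusters, 1:1; 5% error; 80% power; 21% prevalence; a 5-point difference; 1,767 children per arm, so 1,767 / 10 = 176.7 per cluster on average; monitoring threshold p < 0.001 plus a gap of at least 5 points. Assumed, because not given: two-sided tests, ICC, CV of cluster size, low-MUAC prevalence, and no covariates.

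**Step 1: the plan's own figure.** For 21% against 16%, the individually randomised size is
n = [1.96·√(2·0.185·0.815) + 0.8416·√(0.21·0.79 + 0.16·0.84)]² / 0.05² = 946 per arm.
The implied design effect is 1,767 / 946 = 1.87, so with equal clusters the ICC is (1.868 − 1) / 175.7 = 0.0049 (0.0040 at CV 0.5). For 26% against 21%, n = 1,128, the design effect is 1.57 and the ICC 0.0032. The 1,767 is thus consistent with an ICC of about 0.003–0.005, but it cannot be confirmed, because the ICC has to be chosen to fit.

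**Step 2: analytic size with 18 degrees of freedom.** The true size of a nominal z test is P(|t18| > c·√f), where c is the normal critical value (1.96 or 3.29) and f the relative downward bias of the variance. A plain sandwich with 10 equal clusters per arm has f = 9/10.

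| Variance | f | Nominal 5% | Nominal 0.1% |
|---|---|---|---|
| Unbiased, normal reference | 1 | 6.6% | 0.41% |
| Sandwich × 20/19 | 0.947 | 7.3% | 0.49% |
| Plain sandwich | 0.9 | 7.9% | 0.59% |

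**Step 3: simulation under the null.** Beta-binomial data, 20 clusters, logit GEE with a normal reference, prevalence 12% or 21%, ICC 0.006–0.05, mean cluster size 60–176, 40,000 runs per setting.

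| Variance | Nominal 5%, CV 0–0.5 | CV 0.8 | Nominal 0.1%, CV 0–0.5 | CV 0.8 |
|---|---|---|---|---|
| Plain sandwich | 7.9–9.8% | up to 11.3% | 0.56–0.95% | up to 1.4% |
| Sandwich × 20/19 | 7.3–9.0% | up to 10.5% | 0.49–0.81% | up to 1.2% |

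The excess changed little at cluster means of 60–100. That matters because the primary contrast uses only cash-receiving households, so its clusters may hold fewer than 176.7 children.

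**Step 4: the full stopping rule.** How far the 5-point condition helps depends on the standard error of the difference, √(2p(1 − p)·DE / (10·m)), with DE = 1 + (m − 1)·ICC. With m = 177:

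- p = 12%, ICC 0.005: DE = 1.88 and SE = √(2·0.1056·1.88 / 1,770) = 1.50 points. A 5-point gap is 3.34 SE, so the gap is itself about as demanding as p < 0.001.
- p = 18.5%, ICC 0.005: SE = 1.79 points and the gap is 2.79 SE, so it helps in part.
- p = 12%, ICC 0.02: DE = 4.52, SE = 2.32 points and the gap is 2.15 SE, so it adds little.

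Simulation agrees. At 18.5%, ICC 0.005 and mean size 177, the p-value alone crosses in 0.58% (CV 0) and 0.73% (CV 0.4) of null looks, and the full rule in 0.25% and 0.33%. At 12%, with the same ICC and size, the full rule gives 0.08%; at 10%, 0.02–0.06%. With ICC 0.02 or clusters of 60 it is mostly 0.4–0.8%. It reaches about 1.0% with higher ICC and unequal clusters, and 1.2% at CV 0.8.

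**Step 5: after correction, with a t reference on 18 df.** Mancl-DeRouen gives 3.9–5.0% at nominal 5% and 0.05–0.20% at nominal 0.1%. Kauermann-Carroll gives 5.1–6.8% and 0.09–0.31%. A cluster-summary t-test gives 4.7–5.3% at nominal 5%.

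**Step 6: power.** A design with exactly 80% power under normal quantiles has non-centrality 1.960 + 0.842 = 2.802. Against t18 (critical value 2.10) the power is 75.5%. Restoring 80% needs a non-centrality of 2.963, that is (2.963 / 2.802)² = 1.12, or about 12% more information.

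**The case against.** A reader might infer that the trial uses uncorrected GEE and that its primary error rate therefore exceeds 5%. The article does not say that. It names GEE and stops there, and the choice of variance estimator is the kind of detail a journal article can leave to an analysis plan that is not shown. This objection stands, and it makes the primary half of the point conditional. It does not reach the safety half, where the article itself names an asymptotic reference.

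A reader might also conclude that the stopping rule fires 5 to 11 times too often. That range belongs to the p-value alone, at an assumed prevalence of 18.5% and CV up to 0.6. It leaves out the 5-point gap, and the monitored quantity is low MUAC, whose prevalence is not given. With the gap included, the excess can disappear in favourable settings. Nor is 0.1% a claimed false-stop probability: it is a p-value threshold applied at each of two looks, and two looks alone allow up to 0.2%. Even the worst rates are about 1% per look, a modest absolute risk.

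Finally, the loss of power assumes normal quantiles. The cited sample size method for cluster trials may already allow for few clusters, and the article does not let us tell.

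**Conclusion.** The point holds in this form. If the GEE analysis is run without a small-sample correction, its true type 1 error is about 7–10%; every uncorrected setting examined exceeded 5%. The Wald chi-square named for monitoring has a true tail error of about 0.4–1.0% at nominal 0.1%. Under the complete stopping rule the per-look false-stop rate is usually about 0.3–1.0%, dropping to about 0.1% or less with low ICC, low prevalence and large clusters.

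The direction follows from the 20 clusters alone. The exact sizes rest on assumed ICC, CV and prevalence, beta-binomial clustering, two-sided tests and no covariate adjustment. The documents do not show that the primary analysis will in fact be uncorrected, or that the stopping rule is always too liberal.

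**What to change.** State one small-sample method for every comparison between arms (cash-receiving households, non-beneficiary households, age strata) and for the June and July monitoring p-value. Suitable choices are GEE with a bias-corrected variance and a t reference on 18 degrees of freedom (clusters minus cluster-level parameters), or a cluster-level t-test or permutation test. Mancl-DeRouen is preferable to Kauermann-Carroll, which stays slightly liberal when clusters are unequal. If the analysis plan already specifies such a correction for the primary test, confirm it and extend it to the monitoring test. The stopping thresholds stay as they are; only the way the p-value is computed changes.

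The cost is wording in the analysis plan, plus a restatement of power. If the sample size used normal quantiles, power at the planned size is about 75% rather than 80%, a loss of 4–5 points. State the ICC and CV used, so that this can be checked.

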### Ethical considerations

The study protocol was approved by two independent ethics committees; the Comité Consultatif National d'Ethique at the Ministry of Health in Niger (ID number 021/2014/CCNE).and the University College London Research Ethics Committee (project ID 6543/001). This study is also registered with ISRCTN (ISRCTN25360839). Informed consent procedures described above will allow individual participants to decline to participate. Regardless of whether potential participants consent to take part in the study, the study teams will offer to screen women and children in the sampled households for acute malnutrition and anaemia and refer them to health facilities for treatment according to local diagnostic criteria.

Trial safety will be monitored by measuring MUAC in children brought to the cash distributions in June and July. Our stopping rule will be a significant difference of ≥5 percentage points in the prevalence of low MUAC between arms at either time point, with a *p* < 0.001. Analysis will be conducted using the Wald chi-square test in Stata 13, adjusted for cluster, age, and sex.

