### Interventions

The selection of households that will be eligible to receive one of two UCT interventions will take place in a two stage process that is undertaken by Concern Worldwide as part of their normal humanitarian programming. First, villages will be targeted for UCT interventions based on their perceived vulnerability to food insecurity. Then, within the targeted villages, a wealth ranking is assigned to households using a household survey approach.^3^ This draws on the principles of HEA and has been standardised among NGOs in Niger [26]. Household with a very poor ranking are targeted for cash transfers.

The control intervention is a standard UCT package delivered by Concern Worldwide in Niger as a part of their humanitarian programmes. Each selected household receives 32,500 FCFA^4^ a month, which is given in cash to female representatives who must attend a cash distribution point every month, from June to September. Cash distribution points are sited in villages so that beneficiaries do not have to travel more than 5 km. The total seasonal cash transfer is 130,000 FCFA. The cash amount is calculated by the government to allow purchase of a food basket similar to the World Food Programme (WFP) household ration that will meet 75 % of the daily kilocalorie needs of a household of seven people. Cash is given to women on the assumption that they will be able to influence its use to the benefit of children. The cash transfer is manual because the mobile phone network does not support money transfers. A nutrition supplement is given to any pregnant and lactating women (PLW) and children 6–23 months old in the cash receiving household regardless of their nutritional status, as long as they attend on the distribution day. At the distribution, women must attend a health, hygiene, and nutrition education session and PLW and children are screened for acute malnutrition using Mid Upper Arm Circumference (MUAC) and referred to supplementary or therapeutic feeding programmes according to referral criteria. Concern Worldwide also undertakes community sensitisation on the objectives of the cash programme, including suggestions to use the cash to buy food for children.

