The modified intervention gives the same total amount of cash to households, but over a longer period of time. A UCT of 21,500 FCFA is given manually to female household representatives who must attend a cash distribution point every month from April to September (22,500 FCFA is given in June). The total seasonal cash transfer is the same as for the standard intervention (130,000 FCFA). The intervention is the same as the standard intervention in all other ways and nutrition supplements are only given between June and September. Figure 2 illustrates the intervention components and timings, alongside the data collection plans.

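### The June/July stopping rule states p < 0.001 but, with about 20 clusters and no few-cluster correction mentioned, its Wald test delivers roughly 0.5%; it also names no direction, although one arm is unpaid before the June look

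*Protocol article*

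**What the plan says.** All references are to the protocol article; no SAP is shown.

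- **Looks and population** (Ethical considerations): "Trial safety will be monitored by measuring MUAC in children brought to the cash distributions in June and July".
- **Trigger** (same section): a significant difference of 5 or more "percentage points in the prevalence of low MUAC between arms at either time point", "with a *p* < 0.001". Neither arm is named as the one whose excess counts.
- **Test** (same section): "Analysis will be conducted using the Wald chi-square test in Stata 13, adjusted for cluster, age, and sex".
- **Clusters** (Study design and randomisation): "There will be around 20 cash distribution points, which will result in each intervention group having 10 clusters".
- **Payment calendar** (Interventions): standard-arm women are those "who must attend a cash distribution point every month, from June to September"; modified-arm women are those "who must attend a cash distribution point every month from April to September (22,500 FCFA is given in June").

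The primary comparison is made at end-line, with data collected in September-October (Data collection; Data analyses).

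**The concern.** There are two separate matters.

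**The threshold.** A Wald chi-square test treats the cluster-based variance as if it were known. With about 20 clusters it is estimated on roughly 18 degrees of freedom, and the discrepancy is greatest far out in the tail, which is where a 0.001 criterion lies. A monitoring committee reading p < 0.001 would then hold weaker evidence than the number suggests.

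**What the June look compares.** Children are measured at the distributions. By the June distribution the modified arm has received the April and May payments and the standard arm is about to receive its first. The two regimens are of equal value only once both are complete in September. Because the rule is undirected, an early difference in favour of the modified arm would meet it just as an early harm would. A stop in June would come before the standard regimen had been delivered, and the end-line question could not be answered.

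**Working it through.** **1. Inputs**

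From the protocol: two looks; p < 0.001; at least 5 points; 10 clusters per arm; 1,767 children per arm for 80% power against a 5-point difference, with end-line prevalence 21% (Sample size calculation).

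Not in the protocol, so assumed and varied: children measured per arm at a look (600-900), mean low-MUAC prevalence (8-18.5%), ICC (0.005-0.02).

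*ICC anchor.* For 21% against 16%, 5% two-sided error and 80% power, individual randomisation needs 946 per arm. Then 1,767/946 = 1.87 and (1.87 - 1)/(176.7 - 1) = 0.0049. This reads the 5 points as a reduction with equal cluster sizes, and it concerns the primary outcome, not low MUAC. The protocol gives no ICC, so 1,767 cannot be reproduced exactly.

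*Attendance.* The target of 3,500 children includes children from households not receiving cash, and only children brought to distributions are measured. The number per arm must therefore be below 1,750.

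**2. What the threshold delivers**

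- Two-sided p = 0.001 on the normal distribution: cut-off 3.29.
- The same 3.29 on t(18): p = 0.0041.
- The t(18) cut-off for p = 0.001: 3.92.
- Two looks, treated as independent: nominal 1 - 0.999² = 0.002; on t(18), 1 - (1 - 0.0041)² = about 0.008.

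Simulation under no difference: beta-binomial, 20 equal clusters of 60 or 90 children, prevalence 10-18.5%, ICC 0.005-0.02, 200,000 trials per setting.

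| Test | p < 0.001 | p < 0.001 and at least 5 points |
|---|---|---|
| Cluster-robust Wald against 3.29 | 0.5-0.6% | 0.2-0.6% |
| Corrected variance against t(18) | about 0.1% | 0.06-0.1% |

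At 177 children per cluster, 10% prevalence and ICC 0.005, the 5-point clause brings the uncorrected rate down to 0.02%, because a chance 5-point difference is then rare.

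**3. Chance of firing if a true early difference exists**

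SE = sqrt(2p(1 - p)[1 + (n/10 - 1)ICC]/n), where n is children per arm and p is mean prevalence. The observed difference must reach the larger of 5 points and 3.29 × SE. Normal approximation, one look:

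| n per arm | p | ICC | Observed difference needed | P(fire), true 5 points | P(fire), true 2.5 points |
|---|---|---|---|---|---|
| 600 | 12% | 0.005 | 7.0 | 17% | 1.7% |
| 600 | 12% | 0.02 | 9.1 | 7% | 0.9% |
| 600 | 18.5% | 0.005 | 8.4 | 9% | 1.0% |
| 600 | 18.5% | 0.02 | 10.9 | 4% | 0.6% |
| 900 | 12% | 0.005 | 6.1 | 28% | 2.7% |
| 900 | 12% | 0.02 | 8.4 | 9% | 1.0% |
| 900 | 18.5% | 0.005 | 7.2 | 15% | 1.6% |
| 900 | 18.5% | 0.02 | 10.0 | 5% | 0.7% |

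Example: n = 900, p = 12%, ICC 0.005 gives SE = 1.84 points; 3.29 × 1.84 = 6.06; P = Φ((5 - 6.06)/1.84) = 0.28. At 8% prevalence the range for a true 5 points is higher, 13-49%.

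**4. Exposure at each look**

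Payments received before the measurement: June, two (April, May) against none; July, three against one.

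**The case against.** **The test is already cluster-adjusted, and a condensed article may leave a small-sample correction to the full protocol or SAP.** The first part is right: it would be wrong to say that the test ignores clustering. The second has force, but the article itself fixes the test, the software and the p-value, and that combination does not deliver the stated level unless a correction is added. Its effect is modest: false stops stay at about 0.6% or less per look.

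**The rule may be two-sided on purpose.** Deterioration in the arm not yet paid could itself be a safety concern, and two ethics committees approved the protocol. This stands as a possible rationale. It is why the point asks for the intent to be stated and does not say which direction should count.

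**The full effect is unlikely to be present by June.** The 5 points in the sample size section refer to acute malnutrition at end-line, defined by weight-for-height, not to low MUAC after two of six payments. This stands. With half the effect the chance of firing is about 0.6-2.7% in the settings tabulated.

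**Stronger readings that a reader might infer.** One is that the standard arm goes wholly unscreened before June. The protocol does not support this: study teams offer screening and referral to sampled households in both arms. Only April-May screening at distributions differs, and that is itself inferred from the payment calendar. Another is that adjusting for cluster makes the arm effect inestimable. That would require cluster as a fixed effect, which the text does not say; Data analyses speaks of adjusting for within-cluster correlation.

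**Conclusion.** The point holds in two parts.

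1. As described, the monitoring test runs at about five times its stated level: 0.5-0.6% per look against 0.1%, or 0.2-0.6% once the 5-point clause is added at 60-90 children per cluster. This assumes a cluster-robust Wald statistic read against the normal distribution. The threshold is misstated, but this is not a main cause of halting.

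2. The rule does not say which difference is the safety signal, and the June look compares an arm with two payments against one with none. For a true 5-point early difference the chance of firing at one look is roughly 5-30% (600-900 children per arm, mean prevalence 12-18.5%, ICC 0.005-0.02), higher if low MUAC is rarer and much lower if only part of the effect has appeared. Attendance, prevalence and ICC are all assumptions.

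A reader might conclude that the trial is likely to be stopped in June. The protocol does not support that; it shows only that an early benefit could trigger a rule presented as safety monitoring.

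**What to change.** **Test.** Compute the monitoring p-value with a bias-corrected cluster-robust variance referred to t with 18 degrees of freedom, or with a permutation test over the 20 clusters (C(20,10) = 184,756 allocations, enough to resolve p < 0.001), with arm as a cluster-level factor. The cost is a different analysis command and no new data. The downside is some loss of sensitivity: on t(18) the cut-off rises from 3.29 to 3.92, so at the same SE the observed difference needed rises by about 19% (3.92/3.29 = 1.19), for example from 6.1 to 7.2 points with 900 children per arm, 12% prevalence and ICC 0.005.

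**Wording.** Reconcile the monitoring rule in Ethical considerations with the two payment calendars in Interventions: state which difference counts as the safety signal, and how the June look is to be read when one arm has not yet been paid. That choice belongs to the investigators and those responsible for safety oversight. The cost is a few sentences.
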